### Data analysis for cost-effectiveness analysis

#### Vaccine efficacy estimation

We will utilize Poisson regression to calculate the rate ratios (RRs) of participants who will receive influenza vaccination compared to those who will not. In the final model, we will include all the variables that will incorporate all variables that exhibit a confounding effect or demonstrate statistical significance at a significance level of 5%. The investigation of additional potential effect modifiers will be conducted by incorporating interaction terms. We will calculate vaccine effectiveness with 95% CI for each risk group ( (1 - RR) * 100) [72].

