### Study design

We will conduct our study leveraging the ongoing HBIS platform, a network of nine tertiary-level hospitals across Bangladesh [19, 25]. The structure and operational aspects of the HBIS platform have been previously discussed [19, 25]. Our study design will be quasi-experimental. To meet the vaccine acceptability objective, we will collect data on participants’ health beliefs, barriers, and vaccination intentions using the health belief model (HBM) from patients meeting criteria for high-risk populations attending two public tertiary-level hospitals. To meet the influenza vaccination cost-effectiveness objective, in one of the two hospitals, we will conduct an influenza vaccination campaign before the influenza season, where the vaccine will be offered free of cost to high-risk patients, and in the second hospital, vaccination will not be offered. Both the vaccinated and unvaccinated participants will then be followed-up once a month for one year to record any influenza-like illness, hospitalization, and death. Additional data for vaccination cost-effectiveness objectives on direct and indirect costs associated with influenza illness will be collected from ILI and SARI patients at one public and one private hospital. To meet the required capacity for a facility-based influenza vaccination objective, we will collect secondary data, including the Statistical Yearbook of Bangladesh 2020, as represented in Table 1 [26–28].

**Table 1 Tab1:** Assumptions and data sources by each target group

Target Group	Assumption and data sources
Children 6 months to 8 years, influenza vaccine doses	Two doses will be delivered, each four weeks apart [31, 32]. Data of the total number of < 5 years children will be adopted from the Statistical Yearbook of Bangladesh 2020 [26]. Monthly the number of children < 8 years visited hospitals will be collected from respected hospitals or respective District Civil Surgeon Office [29, 30, 33].
Pregnant women’s influenza vaccine doses	One dose to all pregnant women (any trimesters). The crude birth rate is assumed to be 21.9% (BDHS 2017-18) [34]. Influenza vaccines were distributed evenly across the childbearing years 15 through 49 [34]. Data on the total number of women of childbearing age (15–49 years) will be collected from the Statistical Yearbook of Bangladesh 2020 [26]. Monthly pregnant women who visited hospitals will be collected from respective hospitals or respective District Civil Surgeon Office [29, 30, 33].

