### Study setting

We selected study hospitals considering several factors. Firstly, we will use the hospital-based influenza surveillance (HBIS) platform to conduct this study. We have chosen Rajshahi Medical College Hospital and Khulna Medical College Hospital for our study activities on high-risk groups’ vaccine acceptability and cost-effectiveness. We will enroll Severe acute respiratory illness (SARI) and influenza like illness (ILI) patients identified from the HBIS platform to meet our study objectives. We will also collect influenza virus test results from the HBIS platform and data on influenza illness episodes’ costs from the influenza-positive SARI and ILI patients. This approach will save influenza virus testing costs not allocated in the current study budget. Secondly, to assess the outcome of influenza vaccination, we plan to enroll patients from public tertiary-level hospitals (one treatment/vaccinated and the other control hospital) to minimize baseline differences between the treatment/vaccinated and control arm. Thirdly, we have chosen Ragib-Rabeya Medical College & Hospital to represent public and private healthcare facility cost differences while estimating the costs of influenza illness. A brief description of the study sites’ bed occupancy rate and average monthly admission are represented in Table 2 [29, 30].

**Table 2 Tab2:** Demographic characteristics of the study hospitals

Study sites	Bed occupancy rate (%)	Total no OPD visits	Total number of PNC visits	Total number of admission	Middle wealth quantile
Rajshahi Medical College Hospital	198.05	114,818	2,405	22,022	24.1%
Khulna Medical College Hospital	275.00	35,311	991	8,859	24.8%
Jalalabad Ragib-Rabeya Medical College & Hospital	NA	NA	NA	NA	15.8%

Source: Local health bulletin October 2022

OPD = outpatients care department; PNC = post-natal visit

Note: a bed occupancy rate greater than 100% indicates that these hospitals receive and care for more patients than their capacity

Study sites for influenza vaccine acceptability, health beliefs, barriers:

We will conduct a health belief model (HBM) survey in two conveniently selected hospitals:

Rajshahi Medical College Hospital, Rajshahi.Khulna Medical College Hospital, Khulna.

Study sites for influenza vaccination cost-effectiveness objective:

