### Follow-up of vaccinated and unvaccinated participants

icddr,b field staff will follow up with vaccinated and unvaccinated study participants bi-weekly through mobile phone for the entire influenza season. During the follow-up, data will be recorded on health outcomes, including respiratory symptoms, influenza-like illness, hospitalization, and death. To minimize loss to follow-up, icddr,b field team will contact the cohort member at their convenience. icddr,b field team will use the alternative number collected during enrolment where they cannot reach their regular mobile phone number. At the end of one follow-up interview, the interviewee will be consulted about the convenient time of their upcoming follow-up date. After taking these approaches, if it is impossible to reach a cohort member for three follow-up schedules, he/she will be declared lost to follow-up case. For the loss to follow-up case, icddr,b field team will place notes on their data identification number. The study flow chart is shown in Fig. 2.

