#### Quantitative variables

We will conduct a thorough literature review to help us choose the quantitative variables for our study, drawing upon a range of sources [5, 31, 36–44]. The variables will be categorized into three broad categories. Firstly, we will encompass sociodemographic variables, which consist of a wide range of sociodemographic data related to the specific high-risk group being studied. Secondly, in the medical history section, we included variables regarding the medical history of individuals at high risk and any common signs and symptoms they experienced in the previous 30 days. The third category includes direct and indirect cost components related to using medical resources for SARI and ILI. These variables include expenses that occur before, during, and after receiving treatment for SARI and ILI. This provides a thorough understanding of the economic factors associated with these conditions.

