## Discussion

While research indicates that influenza imposes a significant disease burden and economic costs on high-risk populations in low- and middle-income countries (LMICs), including Bangladesh, influenza vaccination has not received adequate attention in these regions until 2023 [9, 15, 16, 44, 82]. Similar to other low- and middle-income countries (LMICs), Bangladesh has experienced low adoption of influenza vaccines and a dearth of country-specific evidence regarding the effectiveness and cost-effectiveness of vaccination programs targeting high-risk groups [10, 16].

In order to address the existing data gaps and support the development of a national influenza vaccination policy, the present study aims to evaluate the acceptability, cost-effectiveness, and necessary infrastructure for implementing a seasonal influenza vaccination program that targets explicitly high-risk populations in Bangladesh. The study will be carried out in three tertiary-level teaching hospitals situated in Bangladesh. In this study, we will employ the health belief model (HBM) framework to assess the acceptability, health beliefs, barriers, and intention to receive the influenza vaccine. To assess the efficacy of the influenza vaccination, we will offer the vaccine for free to study participants and then follow up with them biweekly for one year. We will also employ a deterministic Markov decision-analytic model to evaluate the cost-effectiveness of facility-based vaccination in Bangladesh.

In early 2019, the WHO published a Global Influenza Strategy for the period of 2019–2030 with the aim of safeguarding individuals across all nations against the potential risks posed by influenza [83]. In order to effectively prevent and control influenza and attain a significant level of progress by the year 2030, it is imperative to prioritize the promotion and implementation of influenza vaccination strategies among high-risk populations, particularly in low- and middle-income countries such as Bangladesh.

One notable limitation of this study is its exclusive focus on two tertiary-level healthcare facilities. In future research, it is strongly recommended to broaden the scope by incorporating a more diverse range of healthcare facilities to enhance the generalizability of the findings.

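### The effectiveness rate ratio has no named outcome or risk window and follow-up length is contradictory; over a full year, off-season illness would pull effectiveness towards zero

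*Protocol article*

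**What the plan says.** **Estimator.** The analysis section on vaccine efficacy states: "We will utilize Poisson regression to calculate the rate ratios (RRs) of participants who will receive influenza vaccination compared to those who will not". Effectiveness is (1 - RR) × 100 with a 95% CI, one per risk group. Covariates enter if they confound or reach 5% significance, and interaction terms are mentioned only in general. No event, risk window or season variable is named.

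**Follow-up.** Three descriptions do not agree:
- Study design, and likewise the abstract, has both cohorts "followed-up once a month for one year to record any influenza-like illness, hospitalization, and death".
- Follow-up of vaccinated and unvaccinated participants: "bi-weekly through mobile phone for the entire influenza season".
- Discussion: "follow up with them biweekly for one year".

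**Outcome.** At the phone contacts "data will be recorded on health outcomes, including respiratory symptoms, influenza-like illness, hospitalization, and death". The sample-size section for effectiveness names efficacy against influenza but takes ILI percentages as event rates (15.30%, 31.23%, 10.97% and 20% by group) and expects 50 to 81% efficacy. Study setting says "We will also collect influenza virus test results from the HBIS platform" and explains that testing costs are not in the study budget.

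**Allocation and entry.** One public hospital vaccinates and the other serves as control. The campaign precedes the season and lasts three months. No enrolment window is given for the control hospital.

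**The concern.** Influenza vaccine cannot prevent ILI caused by other agents, and outside the season nearly all ILI is of that kind. If a year of ILI goes into one rate ratio, the off-season events add about equally to both arms and move the ratio towards 1. The amount depends on how long and how busy the off-season is, which has nothing to do with the vaccine. Effectiveness is a natural input to the cost-effectiveness model, so an understated value could carry into the policy conclusion.

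Two further matters follow from the design. Entry dates may differ between hospitals while risk varies by season, which can bias the ratio separately. And because exposure coincides with hospital, a difference in background ILI between the hospitals cannot be told apart from a vaccine effect within the season.

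**Working it through.** **1. What each follow-up text implies.** Under season-only follow-up all person-time is in season, so there is no off-season dilution and there are no off-season data. Under one year, both exist. The length therefore has to be settled before the estimate has a definite meaning.

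**2. Dilution under one-year follow-up.** Let S be the months in season, r the off-season ILI rate relative to the in-season rate, and e the in-season reduction in ILI. Then

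whole-year effect = 1 - [S(1 - e) + (12 - S)r] / [S + (12 - S)r] = e × s, where s = S / [S + (12 - S)r].

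The relative loss is 1 - s and does not depend on e. The documents give neither S nor r, so these are assumptions:
- Middle case, S = 5, r = 0.5: s = 5/8.5 = 0.588, loss 41%.
- Mildest case, S = 6, r = 0.5: s = 6/9 = 0.667, loss one third.
- Worst case, S = 4, r = 1: s = 4/12 = 0.333, loss two thirds.

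**3. In-season illness that is not influenza.** If a share f of in-season ILI is influenza, e = f × efficacy. Assuming f = 0.25 and efficacy 60%, e = 0.15 in season and 0.15 × 0.588 = 0.088 over the year. In this example the larger step is from 60% to 15%, and limiting the analysis to the season does not undo it. Even 81% efficacy would give only 0.25 × 0.81 = 20% against ILI.

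**4. Does adjusting for time help?** A Poisson model was fitted to expected counts for 12 months, with equal ILI rates in 6 in-season and 6 off-season months (s = 0.5) and a 50% in-season effect.
- No time term: 25%.
- Month main effects added: still 25%.
- Vaccination-by-season interaction: 50% in season, 0% off season.

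**5. Power.** Table 5 does not say whether its numbers are totals or per arm. With the stated inputs (taking 5% as two-sided), children (465) are roughly matched as a total at 60% efficacy (468 to 473), and pregnant women (756) at 60% with continuity correction. The elderly (736) and chronic-disease (610) figures are not reached anywhere from 50 to 81%. The dilution does not depend on this. Power below is for two proportions, two-sided 5%, effective N = N × 0.9/1.2, s = 0.5, a 50% effect on all in-season ILI, and the protocol's ILI percentages taken as annual risks (an assumption).

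| Group | Total N: year / season | Per arm: year / season |
|---|---|---|
| Children | 18% / 34% | 32% / 58% |
| Pregnant women | 20% / 38% | 35% / 64% |
| Elderly | 34% / 61% | 59% / 88% |
| Chronic disease | 47% / 74% | 76% / 96% |

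**6. Hospital difference.** With a true in-season effect of 50% (RR 0.5), a background ILI ratio of 0.8 (vaccinated to control hospital) gives 0.5 × 0.8 = 0.40, an apparent 60%. A ratio of 1.2 gives 0.60, an apparent 40%. The off-season rate ratio would be about 0.8 or 1.2, which would reveal the difference if it persists through the year.

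**The case against.** - **The year is not settled.** The section devoted to follow-up limits it to the season. A reader might infer from the other texts that a full year of ILI is certainly pooled, but the documents do not establish that. This stands, and it makes the dilution conditional.
- **ILI is not named in the analysis section.** If only confirmed influenza counted, off-season illness from other causes would drop out. This stands as a caution. Phone reporting, sizing on ILI rates and the absence of a testing budget still make ILI the likelier reading, and no virus test is described for cohort members.
- **The lack of a calendar-time term is not the cause.** A reader might blame that omission. Step 4 shows otherwise: month main effects leave the estimate at 25%. They are relevant only to differing entry dates.
- **This could be left to an analysis plan.** Risk windows and checks often are, and nothing in the article forbids them. Not using off-season data is a missed opportunity, not an error. But the article itself defines the estimator, leaves its window open and contradicts itself on follow-up.
- **Negative controls can be oversold.** A reader might say the off-season ratio must equal 1. That requires no influenza at all in those months, which the documents do not claim. The medical-history item, "any common signs and symptoms they experienced in the previous 30 days", is weaker still: it is not ILI, and among people attending hospital it reflects their reason for attending.

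**Conclusion.** The point holds in conditional form. The follow-up passages contradict each other, and the effectiveness estimate has no named outcome or risk window. If follow-up is one year and the outcome is unconfirmed ILI, following the plan gives an effectiveness estimate too low by the off-season share of the year's ILI: one third to two thirds over the assumed range, 41% in the middle case. If follow-up is season-only, this loss is zero. The documents cannot fix the size, because they give no season length or off-season ILI rate. Under either reading, an ILI-based estimate measures effectiveness against ILI and is not comparable with the 50 to 81% expected against influenza. A change should be made before analysis.

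**What to change.** 1. Reconcile the abstract, Study design, follow-up section and Discussion on the length and frequency of follow-up.
2. Name the event counted in the effectiveness analysis. If it is ILI, say that in-season ILI from other causes still dilutes the estimate and that it should not be read against the 50 to 81% expectation.
3. Make the primary estimate the rate ratio in person-time during influenza-active periods, defined in advance from the hospital-based influenza surveillance (HBIS) platform, or the in-season term of a vaccination-by-season interaction. Adjust for calendar month to deal with differing entry dates.
4. If follow-up is one year, also report the off-season rate ratio as an approximate negative control for differences between the hospitals.

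**Cost.** Model wording and a link to surveillance dates, with no extra visits. It should be confirmed that activity data cover both cohort hospitals, since the article mentions test results alongside the cost work, whose sites do not include Khulna; failing that, a common definition from the HBIS network could serve. The in-season estimate rests on fewer events and has a wider interval, although in the worked example its power is higher because the effect is not diluted by off-season illness.

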#### Cost-effectiveness estimation

To estimate the cost-effectiveness of our pilot influenza vaccination porgramme targeted for the high-risk group, we will use the built-in formulas of the CETSIV tool. The CETSIV is a Microsoft Excel-based tool designed to analyze the cost-effectiveness of influenza vaccination using a decision tree model [43]. It features built-in formulas for deterministic Markov decision-analytic models to evaluate the incremental costs and DALY of the vaccination compared to a controlled scenario [43]. Besides, we will recheck the outputs by developing a deterministic Markov decision-analytic model to simulate outcomes under alternative assumptions of input parameters. Individual DALYs will be calculated for each risk group’s individual using the WHO global health estimates for DALYs [49]. Incremental cost-effectiveness ratios (ICERs) will be calculated as the ratio of incremental cost over incremental DALYs. We will conduct a probabilistic sensitivity analysis (PSA) to see how parameter estimation precision uncertainty affects the model’s outcome. Since we will develop a cohort-based Markov model, each model had different years of estimation depending on the age at which each cohort enters the mode. Hence, such calculated ICERs will be measured using different future time frames. In order to ensure consistency of ICERs across all cohorts, the discount will be applied to ICERs using the number of years remaining life years. We will assume a life expectancy of 75 and a discount rate of 5%. Identified key parameters will change simultaneously over predetermined probability distribution. The Markov model will be run 1,000 times for each risk group, assuming variations in key parameters using pre-defined probabilities to allow for uncertainty in parameters. If ICER is below less than three times the gross domestic product (GDP) per capita, we will consider the vaccination as cost-effective, as per the WHO standard [73–76]. Also, we will estimate rates of influenza cases averted /outpatient visits averted/hospitalization averted/ deaths averted, or influenza treatment cost or productivity loss averted by influenza vaccination in each risk group using the method described by Meredith et al. 2019 [77].

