For reducing the influenza disease burden, influenza vaccination has demonstrated significant efficacy and cost-effectiveness, particularly within populations at high risk of infection [21, 22]. The immune responses induced by influenza vaccines are typically specific to the particular viral strain. The presence of antibodies specific to a certain type or subtype of influenza virus typically offers minimal or no immunity against other types or subtypes. Furthermore, such antibodies usually do not protect against antigenic variants of the same virus that emerge due to antigenic drift. Vaccination can potentially induce a “back boost” of antibody titers specifically targeting influenza A(H3N2) viruses in the adult population. Influenza vaccines are administered on an annual basis due to the occurrence of antigenic drift and shift. The efficacy of these vaccines, which typically ranges between 40% and 60%, exhibits considerable variation across different settings and influenza seasons [10]. In addition, the findings of a systematic review indicated that out of the 118 studies examined, 22 studies demonstrated that influenza vaccination resulted in cost savings [23]. This study’s findings also stated that there were 13 studies reporting cost-effectiveness ratios of $10,000 per outcome, another 13 reporting ratios ranging from $10,000 to $50,000 per outcome, and three reporting ratios equal to or exceeding $50,000 per outcome [23]. Although the cost-effectiveness of influenza vaccination has been established, it is necessary to note that the applicability of cost-effectiveness parameters may vary across different countries due to variations in influenza disease profiles, unit costs of vaccination, and health system delivery mechanisms [24]. Hence, it is imperative to have country-specific estimates to allocate limited resources effectively.

Bangladesh lacks context-specific data on the acceptability, cost-effectiveness, and vaccination capacity needed for influenza vaccination among the WHO-defined high-risk population, which hinders informed vaccination strategies.

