#### The sample size for the vaccine effectiveness objective

Our primary outcome for health outcome for vaccination is vaccine efficacy against influenza among high-risk group populations. Studies from neighboring countries found that ILI symptoms were 15.30% of children, 31.23% of adults with chronic illness, 10.97% of pregnant women, and 20% of the elderly [68–70]. A systematic review of seasonal influenza vaccine policy, use, and effectiveness also revealed that pooled vaccine effectiveness for high-risk groups in the tropics and subtropics ranged from 48 to 88% (10). We expect a similar vaccine efficacy between 50 and 81% for our study’s targeted high-risk group population. A 5% significance level, 80% power, design effect 1.2, and 10% non-response were used to calculate the required sample size to estimate vaccine effectiveness [65–67]. Table 5 represents the high-risk group’s estimated sample size for vaccine effectiveness.

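### As described, the uncertainty around the ICER leaves out between-season variation in vaccine effectiveness, although effectiveness is estimated from a single season and the plan itself says it varies by season

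*Protocol article*

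**What the plan says.** - **Source of VE.** Study design: "we will conduct an influenza vaccination campaign before the influenza season" at one hospital, with none at the other. Vaccination campaign gives its length as three months. Participants are then "followed-up once a month for one year to record any influenza-like illness, hospitalization, and death" (Study design) or contacted "bi-weekly through mobile phone for the entire influenza season" (Follow-up of vaccinated and unvaccinated participants). On either version, one season is observed.
- **Estimator.** Vaccine efficacy estimation, placed under the cost-effectiveness analysis, uses Poisson regression: "We will calculate vaccine effectiveness with 95% CI for each risk group", with VE = (1 − RR) × 100.
- **Model.** Cost-effectiveness estimation uses the built-in formulas of an Excel tool (CETSIV) and rechecks them with the team's own Markov model, in which "each model had different years of estimation depending on the age at which each cohort enters the mode" (that is, the model). Life expectancy is 75 and the discount rate 5%.
- **Sensitivity analysis.** The same section plans a "probabilistic sensitivity analysis (PSA) to see how parameter estimation precision uncertainty affects" the outcome, with 1,000 runs per risk group. The opening of Methods gives the sensitivity analyses the same purpose.
- **Seasonal variation.** Background puts typical efficacy at 40% to 60%, says that it "exhibits considerable variation across different settings and influenza seasons", and attributes annual vaccination to antigenic drift and shift.

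**The concern.** The rate ratio from one season reflects that season's strain match and virus circulation. Its confidence interval measures how precisely that season's effect was estimated. It does not measure how far that season may lie from the seasons in which a programme would run. If the VE distribution in the probabilistic sensitivity analysis (PSA) is built from estimation precision, as its stated purpose implies, a source of variation that the Background names does not reach the ICER. The results are meant to support a national programme and are judged against three times GDP per capita. The limitation given in the Discussion is the restriction to two facilities; the single season is not mentioned.

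A second point follows from the horizon. The risk groups differ in how long a person stays in them: pregnancy lasts months, and membership of the child group ends after age 8. The section does not say for how many years a group's VE applies. If it were re-applied annually over remaining life, the effect for pregnant women or young children would be used in years when the person is no longer in that group.

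**Working it through.** **No figure to reproduce.** The plan gives no ICER interval, no between-season variance and no PSA distribution. The check therefore asks how wide the sampling interval for VE would be, and how much a between-season component would add.

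**Inputs from the document.** ILI rates 15.30% (children), 10.97% (pregnant women), 20% (elderly), 31.23% (chronic disease); Table 5 sizes 465, 756, 736, 610; design effect 1.2; 10% non-response. The document does not say whether the Table 5 sizes are per arm or two-arm totals, and recalculating them does not settle it: as two-arm totals, children and pregnant women reproduce at VE of about 57% to 60%, but elderly and chronic disease fit no VE in the planned 50% to 81% on either reading. Both readings are shown.

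**Assumptions.** VE 50%; between-season standard deviation τ of log RR. With ln 0.60 − ln 0.40 = 0.405, reading 40% to 60% as a 95% range gives τ = 0.405/3.92 = 0.10, and as ±1 SD gives τ = 0.405/2 = 0.20. That range also contains variation between settings, so neither τ is a measured seasonal value.

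**Formulas.** With e₀ and e₁ the expected events in control and vaccinated arms:
- sampling only: SE = √[1.2 × (1/e₁ + 1/e₀)]
- with seasons: SE* = √[SE² + τ²(1 + 1/T)], where T is the number of future seasons. The first τ² is the observed season's departure from the long-run mean; τ²/T is the departure of the average of T future seasons.
- T = 1, 15 (75 − 60) and 67 (75 − 8).

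**Example, elderly, 736 per arm.** n = 736 × 0.9 = 662.4; e₀ = 132.5; e₁ = 66.2. SE = √[1.2 × (0.01510 + 0.00755)] = 0.165, giving a 95% CI for VE of 31% to 64%. With T = 15:
- τ = 0.10: SE* = 0.196, 27% to 66% (1.19 times wider on the log scale)
- τ = 0.20: SE* = 0.266, 16% to 70% (1.62 times)

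**All groups, VE 50%.** Widening is SE*/SE over both τ values and all three T.

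| Group | Table 5 read as | SE | 95% CI for VE, sampling only | Widening |
|---|---|---|---|---|
| Children | total | 0.335 | 3.5–74.1% | 1.05–1.32 |
| Children | per arm | 0.237 | 20.4–68.6% | 1.09–1.57 |
| Pregnant | total | 0.311 | 8.1–72.8% | 1.05–1.36 |
| Pregnant | per arm | 0.220 | 23.1–67.5% | 1.11–1.64 |
| Elderly | total | 0.233 | 21.0–68.3% | 1.10–1.59 |
| Elderly | per arm | 0.165 | 30.9–63.8% | 1.18–2.01 |
| Chronic | total | 0.205 | 25.3–66.5% | 1.12–1.72 |
| Chronic | per arm | 0.145 | 33.6–62.4% | 1.23–2.22 |

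The upper end needs the larger τ and a single future season.

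**Link to the ICER.** If programme cost dominates, health gain is proportional to VE and the ICER to 1/VE, so VE of 40% instead of 60% raises it 0.60/0.40 = 1.5-fold. If averted treatment costs are netted off and net cost stays positive, the ratio exceeds 1.5.

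**The case against.** The strongest reply is that the article does not confine itself to sampling error. Cost-effectiveness estimation also plans to simulate outcomes under alternative input assumptions, and it draws key parameters from predetermined distributions whose content a condensed article may leave to the full protocol or SAP. This stands in part: a reader might infer that only sampling error will be varied, and the text does not prove that. But neither provision mentions season, and the purpose stated in both places is estimation precision. The point is therefore about that stated purpose, not about an unlisted distribution.

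Second, a reader might infer that the study VE is re-applied every year to age 75. The document does not say so. Differing years of estimation and discounting over remaining life also fit a model that counts life-years lost after one vaccinated season, and the section names the pilot programme as its target. This objection stands, so the horizon is an ambiguity to close and not a demonstrated error. Even on the one-season reading, the result is offered in support of a national programme and lacks seasonal variation.

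Third, the sampling intervals are already wide. At VE 50% every interval in the table contains the whole 40% to 60% range, so a misleadingly tight PSA result is not shown. This stands, though not at every VE: at 60%, the per-arm lower limits for elderly and chronic disease are 43% and 46%.

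**Conclusion.** The concern holds in direction, and its size is unknown. One season is observed, the model's horizon varies with entry age, the sensitivity analysis is described by estimation precision, and the plan itself says efficacy varies between seasons. Any between-season variance left out makes the ICER interval too narrow. The widening of about 1.05 to 2.2 times rests on assumed τ of about 0.10 to 0.20, VE 50%, the two readings of Table 5 and T from 1 to 67. In the smaller groups, such as children read as a two-arm total, sampling error dominates and the addition is modest.

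Two stronger readings are not supported. The sample-size section says that "pooled vaccine effectiveness for high-risk groups in the tropics and subtropics ranged from 48 to 88" per cent, and a reader might take this as a seasonal spread that moves the ICER 0.88/0.48 = 1.8-fold. That range runs across risk groups and settings, not seasons. A reader might also conclude that the three-times-GDP verdict would change, but the document gives neither an expected ICER nor a GDP figure, so no effect on that decision can be shown.

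This is a cheap improvement to the model, not a fault that invalidates the study.

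**What to change.** In Cost-effectiveness estimation:

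1. Add a between-season component to the VE distribution in the PSA, on top of the sampling error, and state its assumed size and source. Report ICER scenarios at low and high VE, for example 40% and 60% from the Background. Do not use the 48% to 88% range as a seasonal spread.
2. State for how many years the study VE applies. Restrict it to the vaccinated season and to years in which the person is still in the risk group, and use the remaining-life horizon to count life-years lost from deaths in that season.
3. State in the conclusions that VE comes from one season.

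The cost is changed model inputs and a few extra model runs, with no new participants or data collection. The drawback is a somewhat wider ICER interval.
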